## Data collection in the reference group of healthy children

The assessments done in these children are only those for which no known normal values exist, or for which the result is highly dependent on the examiner, the method used or geography.

These are thymic size (measured by ultrasound), gut permeability (measured by lactulose-mannitol test) and fatty acid status and number of T-cell subsets (measured in a blood sample of 4 ml), all carried out as described above

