#### Secondary objectives:

- To assess child development and physical activity during treatment
- To assess level and predictors of blood essential fatty acids (EFA) on admission, and changes during treatment
- To assess the role of blood EFA for child development and physical activity
- To assess changes in hemoglobin and serum ferritin during treatment
- To compare levels of regulatory T cells and Th17-positive T-cells (T-cell subsets), inflammatory and anti-inflammatory cytokines as well as thymic size in well-nourished children compared to malnourished children with and without oedema, and relate immune parameters to breast feeding and components in breast milk.
- To assess gut permeability by Lactulose-Mannitol Test (LM-test) and gut flora in children with oedematous malnutrition and children without oedema, compared to well-nourished children and relate this to LPS in blood as well as sIgA in breast milk.
- To assess levels of in Tn, ANP and BNP in relation to myocardial function and serum phosphate in malnourished children.

- To assess long-term outcome by morbidity, anthropometry, child development and thymic size after discharge

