### Sample size considerations and data analyses:

Rather than testing a single hypothesis, the study will use an explorative approach to describe the changes in serum phosphate and other parameters during recovery, and the role of various exposure variables such as presence of oedema, HIV, etc. With 120 children in the study, and with 50% with oedema, we will have 90% power to detect a difference of 0.6 SD or more of any normally distributed variable with a 5% significance level. Similarly, with a control group of 20 children, we will have 90% power to detect differences of 0.8 SD or more between children with SAM and control children, of any normally distributed variable. The control group will be crucial, as there are variables for which we have no reference data, hence we need to know the effect of SAM by comparing with the control group.

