## Reference group

Because we wish to assess the effect of malnutrition on a number of physiological parameters, and because some of these parameters are characterized by no known normal values, or the values being highly dependent on the geography, on the examiner, or on the method used, a small reference group of normal children is needed for comparison.

20 healthy children of similar age and sex will be invited to participate from the nearby health centres when they come for routine vaccination, provided that their parents give informed consent for participation. This number of children is calculated from the parameters planned to be studied (thymus size, T-cell subsets, gut permeability and fatty acid status). For these parameters 20 children are anticipated to be sufficient to detect a difference.

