### Blood samples

5 mL of blood will be collected at two different occasions: At admission and at discharge. Of this, 1 ml will be used to measure an inflammatory marker (CRP), markers of kidney function (Creatinin), as well as electrolytes (Phosphate, pH, Ca+, Na, Cl) and albumin. 4 ml will be used to measure levels of different subsets of T-cells as well as levels of anti-inflammatory cytokines, LPS, troponin, ANP and BNP in plasma. A drop of blood will be used for haemoglobin measurement and another drop will be stored on filter paper for analysis of fatty acid status. On additional three days, when moving to a new phase of nutritional treatment and 48 hours after, a small amount (1 ml) of blood will be collected for determination of phosphate, electrolytes and pH. In total, 13 ml of blood will be drawn from each child during the study. *At follow-up after 8 and 16 weeks post-admission, a finger-prick blood sample will be collected for determination of fatty acid status*

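### Two secondary objectives compare cytokines and gut flora with well-nourished children, but the reference group's assessment list includes neither

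*Protocol*

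**What the plan says.** Two of the eight secondary objectives in the Protocol name well-nourished children as a comparator. The immune objective covers T-cell subsets and "inflammatory and anti-inflammatory cytokines as well as thymic size in well-nourished children compared to malnourished children with and without oedema". The gut objective covers permeability and "gut flora in children with oedematous malnutrition and children without oedema, compared to well-nourished children and relate this to LPS in blood".

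The only well-nourished children in the study are the 20 in the reference group. The section on data collection in that group opens with a restriction, "The assessments done in these children are only those for which no known normal values exist" (or for which results depend heavily on examiner, method or geography), and then gives the list: "These are thymic size (measured by ultrasound), gut permeability (measured by lactulose-mannitol test) and fatty acid status and number of T-cell subsets". The Reference group section says that the number 20 was derived from the same four parameters: "thymus size, T-cell subsets, gut permeability and fatty acid status".

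For the malnourished children, the Blood samples section keeps the immune assays apart by name: "4 ml will be used to measure levels of different subsets of T-cells as well as levels of anti-inflammatory cytokines", followed by LPS and the cardiac markers. The Faecal sample section and the overview of assessments place stool collection at admission, start of phase II, discharge and, if possible, the 8-week visit.

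The sample size section says of the reference children: "The control group will be crucial, as there are variables for which we have no reference data".

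**The concern.** An objective that compares a variable between two groups needs that variable in both. Here the objectives and the reference-group assessment list do not match for two variables. A team working from the assessment list would take no stool from a healthy child and order no cytokine assay on that child's blood, and would find the gap only when analysing the objective.

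The two gaps are not equal. Stool that was not collected at the reference child's visit cannot be recovered later. Cytokines are an assay that nobody has been told to run on blood that is drawn anyway.

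At stake are the statements on how cytokine levels and gut flora in malnutrition differ from those in healthy local children. The protocol offers no other source of normal values for either, and it argues that a local group is needed where such values are lacking. A statistical analysis plan could not repair this, because which specimens and assays are taken is fixed in the protocol.

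**Working it through.** **1. The plan's own figure.** The sample size section states 90% power to detect 0.8 SD between children with SAM and 20 controls, for any normally distributed variable. Inputs: n₁ = 20, n₂ = 120, δ = 0.8 SD, α = 5% (two-sided assumed, as sidedness is not stated).

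Power ≈ Φ(δ / √(1/n₁ + 1/n₂) − 1.96)

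- √(1/20 + 1/120) = √0.05833 = 0.2415
- 0.8 / 0.2415 = 3.312, and 3.312 − 1.960 = 1.352
- Φ(1.352) = 91.2%, or 90.8% with the noncentral t distribution

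The companion figure, 60 versus 60 at 0.6 SD (oedema versus no oedema), gives √(1/60 + 1/60) = 0.1826, 0.6 / 0.1826 = 3.286 and Φ(1.326) = 90.8%, or 90.3% with t. Both stated figures reproduce, so the point is not an arithmetic one. The first figure applies only to variables that are measured in the 20 reference children.

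**2. Objectives against planned assessments.**

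| Variable | Objective compares with well-nourished children | In the Reference group sizing list | In the reference-group data collection list | Specimen or examination in reference children |
|---|---|---|---|---|
| T-cell subsets | yes | yes | yes | 4 ml blood |
| Thymic size | yes | yes | yes | ultrasound |
| Gut permeability | yes | yes | yes | LM-test |
| Cytokines, inflammatory and anti-inflammatory | yes | no | no | 4 ml blood drawn, assay not named |
| Gut flora | yes | no | no | none |

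Fatty acid status is on both lists and is measured in the reference group. It plays no part in these two objectives.

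**3. Can the list be read more widely?**

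- The list closes by saying that everything is carried out as described earlier. That governs how the listed items are done and does not add items.
- T-cell subsets do not silently include cytokines. Blood samples and Laboratory tests both name the two separately.
- The Data collection section says that its data come from all participating children. Its time points are hospital phases and follow-up weeks, which reference children do not have, and the reference-group section is the specific rule for them.

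**4. Result.** For gut flora, 0 of 20 reference children have data, so no power can be computed for that comparison. For cytokines, the number with a planned assay is also 0 of 20, but the blood exists.

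**5. A related gap on the malnourished side.** The immune objective promises inflammatory and anti-inflammatory cytokines, whereas Blood samples names only the anti-inflammatory ones: "4 ml will be used to measure levels of different subsets of T-cells as well as levels of anti-inflammatory cytokines". Copying that panel to the reference children would therefore not, as written, deliver the inflammatory half of the comparison.

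**The case against.** The strongest reply is that the cytokine gap is a drafting omission. Reference children give 4 ml of blood. In the malnourished children a 4 ml portion serves T-cell subsets, cytokines and LPS together, and the Laboratory tests section treats T-cell subsets and cytokines as one group of immune parameters at one laboratory. That is a fair reading of what was probably intended. It is why the cytokine point is an unnamed assay and not missing material. It does not remove the point, because the reference-group section restricts its list and leaves cytokines out, and it does nothing for stool.

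Four stronger readings are tempting, and the documents do not support them:

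- *That an LPS comparison with healthy children is also lost.* The gut objective only relates the gut findings to LPS in blood. LPS is measured in the malnourished children, so the association can be examined among them.
- *That the tolerance hypothesis rests on the cytokine contrast.* The background section makes T-cell subsets the central feature to assess and takes raised regulatory T cells as support for the hypothesis. Those cells are measured in the reference group. Cytokines enter as the mouse evidence from which the hypothesis arose.
- *That the two objectives cannot be answered at all.* Both also contrast children with and without oedema, at about 60 versus 60, and that contrast needs no reference children.
- *That the 90% power statement is wrong.* It is generic and reproduces. The protocol gives no power figure specific to cytokines or gut flora.

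It is also fair to say that the study calls itself explorative and that these are parts of two secondary objectives. That bears on severity and does not resolve the mismatch.

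**Conclusion.** The point holds in a limited form. The gut flora gap is unambiguous, since the comparison is promised and no specimen is planned from any of the 20 reference children. The cytokine gap is real on the text as it stands, but can be closed without drawing more blood.

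The severity is moderate. Only the well-nourished arm of two variables, within two of eight secondary objectives, is affected. The primary phosphate objective and the reference comparisons of T-cell subsets, thymic size, gut permeability and fatty acid status are unaffected.

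The conclusion rests on two readings: that the reference-group list is closed, as its restricting wording and the matching list in the Reference group section indicate, and that the 20 reference children are the only well-nourished children studied.

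**What to change.** Reconcile Secondary objectives, Reference group, Blood samples and Data collection in the reference group before reference children are enrolled.

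1. **Cytokines.** State in the reference-group data collection section that inflammatory and anti-inflammatory cytokines are assayed on the 4 ml sample already drawn, and name both types in Blood samples. Add cytokines to the parameters listed in Reference group. Cost: assays on 20 existing samples and no extra blood for reference children. If this is not wanted, remove the well-nourished comparison for cytokines from the objective, which costs only a wording change.
2. **Gut flora.** Either remove the well-nourished comparison for gut flora from the gut objective, keeping it for permeability, or add one stool sample of about 1 g per reference child. The first costs a wording change. The second means 20 non-invasive samples and their analysis, but it is a new procedure in healthy children recruited at vaccination visits. It therefore needs a change to the consent information and ethics approval, and should be left to the sponsor.

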## Data collectors

All measurements and questionnaires will be performed by PhD or Masters students, medical doctors, trained research nutritionists, nurses or health workers. Standard operational procedures (SOP) will be followed for all activities stated.

## Laboratory tests

Haemoglobin and CRP will be measured on the local lab of MNU, using bed-side test devices. These will be calibrated regularly using test-samples of known values.

Other lab analyses will primarily be conducted by MU-JHU Core Laboratory and Infectious Diseases Institute (IDI) – Mulago hospital complex. This is a research lab supported by John Hopkins University which is accredited by College of American Pathologists (CAP) with currently on-going quality control and certified for quality and GCLP. For quality control, a few samples are planned to be

double-analysed here as well as in a collaborating laboratory in Mwana, Tanzania, which has extensive expertise in measuring phosphate.

Laboratory tests not available in Uganda will be shipped to laboratories abroad for analysis.

The analyses of fatty acids will be done in Canada at University of Waterloo, Department of Kinesiology, a lab which has developed a pioneering method of assessing fatty acid status on a dried blood spot on filter paper.

The analyses of immune parameters (T-cell subsets and cytokines) will be analysed in the Department of Infectious Disease, Copenhagen University Hospital, Hvidovre. This is a certified biosafety level 2 laboratory, with advanced multi-colour flow-cytometry. It has on-going quality control, and is accredited by Joint Commision International.

The analysis of cardiac enzymes will be done at Department of Biochemistry at Rigshospitalet, Copenhagen, the National Referral Hospital of Denmark, which also has current internal and external quality control.

Analysis of lactulose-mannitol ratio and stool microbiota will be done at Department of Human Nutrition, University of Copehagen. This lab has on-going quality control and extensive experience with the mentioned analyses.

### **Data analysis**

The primary outcome of the study is level of and changes in serum phophate during treatment, while the results of the other assesments (child development, immune function, heart function, gut permeability) are secondary outcomes.

Data will be analysed using the intercooled version of the statistical software package Stata version 12 (Stata/IC) (StataCorp LP, College station, Texas, USA)). Baseline values of serum phosphate and other exposures will be presented as mean  $\pm$ sd and differences between categories of exposure variables will be analyzed by t-tests and one-way analysis of variance. Final multivariable models will be developed with serum phosphate and other baseline characteristics as outcome, and oedema, HIV and other factors as predictors, while controlling for age and sex. To assess the changes over time and the factors affecting it, repeated measures of serum phosphate and other variables will be analyzed using multilevel mixed-effects linear regression model by using xtmixed.

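### For the 6:1 comparison of children with severe acute malnutrition (SAM) with the reference group, unequal-variance methods would be a cheap improvement, and the common-SD condition behind the 90% power should be stated

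*Protocol*

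**What the plan says.** The sample-size section of the protocol makes two power statements. The first compares children with and without oedema, taking half of the 120 to be affected, and says that "we will have 90% power to detect a difference of 0.6 SD or more". The test level there is 5%, and the claim is made for every variable that follows a normal distribution. The second concerns the reference group: "we will have 90% power to detect differences of 0.8 SD or more between children with SAM and control children". It has the same breadth, and the 5% level is carried over to it by implication. Both differences are given in units of a single SD.

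The Reference group section says that "20 healthy children of similar age and sex will be invited to participate". It ties this number to thymus size, T-cell subsets, gut permeability and fatty acid status, and says that normal values are unknown for some of the parameters. The Secondary objectives include a three-way comparison of well-nourished children with malnourished children with and without oedema.

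The Data analysis section says of baseline values that "differences between categories of exposure variables will be analyzed by t-tests and one-way analysis of variance". It then plans multivariable models adjusted for age and sex, and mixed models for change over time. It does not mention the reference group, does not say whether the t-tests are pooled or Welch, and does not mention a check of variances.

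**The concern.** With equal groups, pooling the variances does little harm. With 120 against 20, the pooled SD is almost entirely that of the SAM children, while the standard error of the difference comes mainly from the mean of the 20 reference children. If the two SDs differ, the standard error is wrong.

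Nothing in the protocol supports equal SDs. It expects the SAM group to be a mixture: about half with oedema, and some with HIV or severe systemic infection. The reference children are healthy. That could make the SAM SD larger. For thymus size, the atrophy described in the background could make it smaller. The error could therefore go in opposite directions for different outcomes in the same report.

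The sample-size section calls the control group crucial for learning the effect of SAM. At stake are false differences where healthy children vary more, and an overly strict test where they vary less.

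**Working it through.** **Inputs.** SAM n = 120 (60 with and 60 without oedema) and reference n = 20, so the split is 120/20 = 6:1. Alpha is 5%, taken as two-sided because the protocol does not say. The difference is 0.8 SD. Group SDs are not given, so a reference/SAM SD ratio of 0.5 to 2 is assumed, with normal data.

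**1. The plan's own figures, with one common SD.** Noncentrality = d / sqrt(1/n1 + 1/n2).
- 120 v 20: 0.8 / sqrt(1/120 + 1/20) = 0.8 / 0.2415 = 3.31. Power is 91.2% (normal) or 90.8% (noncentral t). Solving for sample size returns 20 controls.
- 60 v 60: 0.6 / sqrt(2/60) = 3.29. Power is 90.8% (normal) or 90.3% (noncentral t).

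Both stated figures reproduce.

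**2. What pooling does to the standard error.** Pooled SE = sqrt{[(119·s1² + 19·s2²)/138]·(1/120 + 1/20)}. True SE = sqrt(s1²/120 + s2²/20). Here s1 is the SAM SD and s2 the reference SD.
- s1 = 1.5, s2 = 1: pooled variance = (119·2.25 + 19)/138 = 2.078. Pooled SE = 0.348 and true SE = 0.262. The effective critical value is 1.96·0.348/0.262 = 2.60, so type I error is about 0.9%.
- s1 = 1, s2 = 1.5: pooled variance = (119 + 19·2.25)/138 = 1.172. Pooled SE = 0.261 and true SE = 0.348. The effective critical value is 1.96·0.261/0.348 = 1.47, so type I error is about 14%.

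**3. Simulation, 120 v 20, 200,000 runs per setting.** Power is shown with the 0.8 SD read as SAM SDs and as reference SDs.

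| Reference/SAM SD | Type I, pooled | Power at 0.8 SAM SD, pooled / Welch | Power at 0.8 reference SD, pooled / Welch |
|---|---|---|---|
| 0.5 | 0.2% | 99% / >99% | 36% / 77% |
| 0.75 | 1.7% | 96% / 98% | 76% / 86% |
| 0.9 | 3.5% | 93% / 94% | 87% / 88% |
| 1 | 5.0% | 91% / 89% | 91% / 89% |
| 1.1 | 6.7% | 88% / 83% | 93% / 90% |
| 1.25 | 9.4% | 85% / 74% | 96% / 90% |
| 1.5 | 14.0% | 79% / 60% | 97.5% / 91% |
| 2 | 21.7% | 70% / 39% | 99% / 91% |

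Welch type I error is 5.0% to 5.1% in every row. Where pooled power exceeds Welch power at ratios above 1, the pooled test is also running above its 5% level, so the gap is not a real advantage.

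**4. The imbalance is the cause.** At 60 v 60 the pooled test stays at 5.1% to 5.2% with SD ratios of 0.5 and 2. The oedema comparison is therefore not affected.

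**5. Three-group ANOVA, 60/60/20, under the null.** Type I error is about 3% when the SAM SD is 1.5 to 2 times the reference SD. When the reference SD is 1.5 or 2 times the SAM SD, it is about 10% and 16%. Welch ANOVA stays near 5%.

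**The case against.** The strongest reply is that the protocol states nothing wrong here. Four parts of it stand.

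- A reader might infer that the plan prescribes equal-variance t-tests. It does not: the term covers Welch as well, and only one-way ANOVA in its usual form assumes a common variance. Naming Stata as the software does not settle the point.
- The methods sentence concerns baseline values by exposure category, and the predictors it goes on to name are oedema and HIV. Applying it to the reference group is an inference. It is a fair one, because the protocol offers no other method for that comparison and a three-way objective is what one-way ANOVA would serve.
- A reader might infer that the 5% level and the 90% power fail. Neither is shown. No SDs are given, and at ratios of 0.9 and 1.1 the pooled type I error is only 3.5% and 6.7%. It exceeds 5% only if healthy children vary more than sick ones. With a larger SAM SD, the loss of power appears when 0.8 SD means reference SDs and vanishes when it means SAM SDs. The printed 90% is right on its own terms.
- The study is exploratory and these outcomes are secondary. The choice between pooled and Welch tests is often left to a statistical analysis plan, which is not shown.

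What the reply does not remove is that the protocol names one-way ANOVA, which is fragile at this split. It also claims the power for "of any normally distributed variable", although normality alone is not enough.

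**Conclusion.** This is a cheap improvement, not a demonstrated error. At 6:1, usual one-way ANOVA, and a t-test if pooled, lose the 5% level when the SDs differ. The size is about 0.2% to 22% for the pooled t-test and about 3% to 16% for three-group ANOVA. These ranges rest on normal data and on assumed SD ratios (0.5 to 2 for the t-test; 1.5- to 2-fold either way for ANOVA), not on figures in the protocol. The 90% power at 0.8 SD holds for one common SD. The protocol leaves unsaid that this is a condition and whose SD defines the 0.8. The point covers thymus size, T-cell subsets, gut permeability and fatty acid status. Serum phosphate, the primary outcome, is not measured in the reference children and is unaffected.

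**What to change.** In Data analysis, state that every comparison involving the reference group uses the Welch t-test, Welch ANOVA for the three-group comparison, and heteroscedasticity-robust standard errors (HC3, given the 20 reference children) in models adjusted for age and sex. In the sample-size section, state that the 0.8 SD and 90% figures assume the same SD in both groups, that power is then about 89% with Welch, and which group's SD is meant if the two differ.

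This takes one sentence in each section and needs no new data or children. The cost is about 2 points of power if the SDs turn out equal (89.0% against 90.8%).
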